## **Study design**

We propose an implementation trial that will compare the uptake of screening at the implementation practices utilising the *universal offer of HPV self-testing* approach, to the uptake of screening from practices utilising current standard of care: cervical cytology alone.

### Implementation trial

#### **Implementation practices**

A representative, random sample of primary care practices from the Mahitahi Primary Health Entity will be invited to participate. These practices will offer HPV-self-testing universally over a two-year period.

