#### **Comparison practices**

Seven similar Mahitahi primary care practices (the comparative practices) who will be business as usual offering cervical cytology screens will be asked for permission to retrospectively access their screening data. De-identified data for the same period as the implementation trial will be requested.

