### Inclusion criteria

The NCSP eligibility policy is that “anyone with a cervix or vagina who has ever been sexually active should be offered three-yearly cervical screening from age 25 to age 69.” For this study all women aged 25.00 to 69.99 years and eligible for cervical screening to prevent cervical cancer in the year of the implementation. Includes first cervical screening test (HPV self-taken or clinician taken swab test, or cervical smear for cytology) for women aged 24.5 years and women who have a routine cervical screening test (HPV self-taken or clinician taken swab test) for cytology up to 6 months BEFORE their cervical screening test due date.

Women who have symptoms raising the possibility of cervical cancer, including post-coital bleeding, unexplained intermenstrual bleeding, any post-menopausal bleeding, unexplained persistent unusual vaginal discharge or unexplained persistent deep dyspareunia should have an HPV test but the focus for these women is primary care follow-up investigation of their symptoms.

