### Sample size

The NSCP coverage report from December 2019 for the Northland DHB shows that approximately 72.5% of women (33,403/46,090) aged 25-69 were screened over a period of 3 years. A total of fourteen practices and 5600 women (seven practices offering HPV-self-testing universally over a one-year period to approximately 2800 women, and seven practices providing routine clinical care

 HDEC amendment approved December 2021

data for approximately 2800 women about cervical cytology uptake) will give 95% power at a one-sided significance level of 2.5% to detect a non-inferiority margin of 10% between the two groups (i.e. the screening rates at participating practices will be no worse than 10% less than the screening rate obtained from the comparative data). This margin of error was chosen as we believe it is the smallest value that is clinically relevant. For this sample size we assumed a screening rate of 72.5% in the comparative data and 72.5% in the participating practices, and an average practice size of 400 participants and intra-cluster correlation coefficient of 0.01.

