### **Stage Two**

To enable availability of research findings in a timely manner to inform the national screening programme the number of practices was increased to 14 practices (seven implementation

practices and seven comparison practices). This will achieve the primary aim of testing the “non-inferiority hypothesis” in 12 months. Please see the “Sample size” section for further detail.

The same methods used above in stage 1 will be used to randomly select an additional three practices for the implementation arm from the remaining eligible practices. The random selection will be stratified by practice size and rurality. Within each of the small-rural and small-urban practices, one practice will be randomly selected (n=2). The third practice will be randomly selected from the large practices. This gives a total of seven practices in the implementation arm.

An additional three practices with similar characteristics to the implementation practices will be asked for permission to retrospectively access data from records obtained through clinical care for comparison to the implementation practices.

At the completion of Year 1 the study will have reached the number of participants needed for analysis. In agreement with the Ministry of Health we will offer HPV self-testing in Year 2 to comparison clinics for up to one year or until the new national screening programme starts. Women will still be asked to complete a consent form as this will be part of the research. The research team will use canSCREEN as the database for this group to ensure clinical safety.

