### Proposed Timeline

Due to COVID19 related delays and a change in leadership at Mahitahi, the first year of the project has been spent preparing for the trial (see chart below). The revised timeline means implementation will run from October/November 2021 year to October 2023. The remaining programme time will be spent analysing and disseminating results.

| Task                                                                                                                                                                                                                                                                                                                                                                                         | Oct 2020 – Oct 2021 | November 2021 – October 2022 | November 2022 – October 2023 | October 2023– Oct 2024 |
|----------------------------------------------------------------------------------------------------------------------------------------------------------------------------------------------------------------------------------------------------------------------------------------------------------------------------------------------------------------------------------------------|---------------------|------------------------------|------------------------------|------------------------|
| 
 
• Ethics
 
• Mahitahi partnership team and champions assembled
 
• Train the trainers
 
• Media/ pamphlets etc
 
• Colposcopy triage confirmed locally and nationally
 
• Regular three monthly meetings with MOH, colposcopists and stakeholders
 
• Steering group and Advisory Board meetings
 
 |                     |                              |                              |                        |
| 
 
• Universal offer of primary HPV self-testing (clinician sampling available if patient wishes)
 
• Agreed triage occurs
 
• Data collection commenced
 
• Ongoing consultation with all stakeholders
 
• Regular progress meetings with local PHE team
 
• Advisory Board meetings
 
               |                     |                              |                              |                        |

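### The protocol gives both one year and two years for the primary comparison, and the two-year text would put Year 2 self-testing into the cytology comparator

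*Protocol*

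**What the plan says.** Two years:
- Protocol, Study design, Implementation practices: "These practices will offer HPV-self-testing universally over a two-year period".
- Protocol, Proposed Timeline: "The revised timeline means implementation will run from October/November 2021 year to October 2023".

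One year:
- Protocol, Sample size: "seven practices offering HPV-self-testing universally over a one-year period to approximately 2800 women".
- Protocol, Inclusion criteria: women must be "eligible for cervical screening to prevent cervical cancer in the year of the implementation".
- Protocol, Stage Two: the expansion to 14 practices is meant to settle the non-inferiority question in 12 months, and the number needed for analysis is reached when Year 1 ends.

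Comparator:
- Protocol, Study design, Comparison practices: seven practices continue with usual cytology, and "De-identified data for the same period as the implementation trial will be requested". No dates are given. The Stage One paragraph on comparison practices repeats the request.
- Protocol, Stage Two: "we will offer HPV self-testing in Year 2 to comparison clinics for up to one year". Women tested under this offer still give consent, because the protocol counts it as part of the research.

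Analysis: the Data analysis section specifies an intention-to-treat comparison, a non-inferiority limit of -10, and a superiority step if non-inferiority is shown. It names no time window.

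**The concern.** The comparator window is defined only by reference to the implementation period, so it inherits that period's ambiguity. Under the one-year text, the comparison practices are offering cytology throughout. Under the two-year text, the same practices may be offering the self-test for part of the window while being analysed as the cytology arm. The Stage Two remark that Year 2 testing belongs to the research makes it harder to argue that Year 2 lies outside the implementation trial. An intention-to-treat rule does not remove crossed-over time.

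Crossover of the comparator moves the observed difference towards zero. In a non-inferiority test this is the unsafe direction when the new approach is truly worse, because a real deficit looks smaller than it is. Comparator data are also collected retrospectively, so the period actually extracted depends on which sentence the data request follows.

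**Working it through.** **Inputs (Protocol, Sample size and Data analysis).** Screening rate 72.5% in both arms; margin 10 points; one-sided 2.5%; power 95%; 7 practices per arm with 400 women each; intra-cluster correlation 0.01.

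**1. Reproduce the plan's own figure.**
- Per arm without clustering: (1.960 + 1.645)² × 2 × 0.725 × 0.275 / 0.10² = 519 after rounding up.
- Design effect: 1 + (400 − 1) × 0.01 = 4.99.
- 519 × 4.99 = 2590 per arm; 2590 / 400 = 6.47, so 7 practices and 2800 women.
- Effective size: 2800 / 4.99 = 561 per arm. SE = √(2 × 0.725 × 0.275 / 561) = 0.0267.
- Power: Φ(0.10 / 0.0267 − 1.96) = 96.3%, or 93.0% with a t reference on 12 degrees of freedom.

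The stated 95% is reproduced. The Sample size section ties it to one year.

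**2. Effect of crossover when self-testing is 10 points worse.** Let f be the share of the comparator's screening opportunity in the window that falls under the self-test offer. The protocol does not give f, so it is an assumption. If comparison clinics offered self-testing for 12 of 24 months, f would be 0.50. Because the offer lasts at most a year, that is the upper case.
- Implementation rate: 0.725 − 0.10 = 0.625. Comparator rate: 0.725 − 0.10f.
- Observed difference: −0.10 × (1 − f).
- SE: √{[0.625 × 0.375 + p_c(1 − p_c)] / 561}, where p_c is the comparator rate.
- Chance of declaring non-inferiority: Φ((observed difference + 0.10) / SE − 1.96).

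| f | Comparator rate | Observed difference | SE | Chance of false non-inferiority |
|---|---|---|---|---|
| 0 | 72.5% | −10.0 | 0.0278 | 2.5% |
| 0.10 | 71.5% | −9.0 | 0.0279 | 5.5% |
| 0.25 | 70.0% | −7.5 | 0.0281 | 14% |
| 0.50 | 67.5% | −5.0 | 0.0284 | 42% |

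If each practice contributed 800 women over two years, the last figure would be 46%.

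**3. Other true differences, f = 0 against f = 0.50, 400 women per practice.**
- True −5: non-inferiority declared in 45% against 77%.
- True 0: 96% in both cases; no effect.
- True +10: non-inferiority is essentially certain either way, but power for superiority falls from 98% to 55%.

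**The case against.** The strongest reply is that the more specific text already points to Year 1. Stage Two says the non-inferiority aim is met in 12 months, and only then introduces the Year 2 offer. The sample size and the eligibility wording also use one year. The two-year sentence describes how long practices offer the test, and a second year has its own purpose, namely the repeat HPV tests after 12 months. No sentence says that Year 2 comparator data enter the primary test. This stands as a statement of probable intent. A reader might infer that the trial plans a contaminated comparison, and the documents do not support that. But it does not remove the conflict: the undated comparator request and the timeline are current text, and the request already names seven practices, so it reflects the expansion.

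Three further limits also stand.
- A reader might infer that crossover always favours non-inferiority. It does so only if self-testing is truly worse. The protocol's own earlier trial, in under-screened Māori women, found the self-test offer reached over 50% against 21%. If that direction holds here, the harm falls on the superiority step.
- A reader might take the 42% as the expected error. It needs a true deficit exactly at the margin, all comparison clinics crossed over for half the window, immediate full effect, and dilution proportional to time. Women screened in Year 1 are not changed by a Year 2 offer, so proportionality is not established.
- A reader might infer that Stage One practices were already testing before Stage Two practices joined, so that no single calendar window exists. The protocol says the original study was under way when practices were added. It gives no testing start dates by stage, so this goes beyond the text.

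The exact analysis window is often left to a statistical analysis plan. Here, though, the protocol states conflicting periods, and a plan that chose one would still disagree with some of its sections.

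**Conclusion.** The protocol is wrong as written: it contradicts itself on the window of the primary comparison. A Year 1 analysis is probably intended, and under it the stated design stands, with 2.5% error at the margin and about 96% power (93% with the t reference). Under the two-year text, false non-inferiority at a true −10 points rises to between about 5.5% and 42% for crossover shares of 10% to 50%. The size is conditional on that text being followed and on the planned rates, practice size and intra-cluster correlation, as well as on the assumed shares and linear dilution. It should be corrected because one stated reading gives a biased primary result.

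**What to change.** State in Data analysis that the primary non-inferiority comparison, and the superiority step that follows it, use one 12-month Year 1 window, given by dates, the same calendar period in both arms, and ending before any comparison practice offers HPV self-testing. State that Year 2 data from comparison clinics are excluded from the primary comparison and that Year 2 data serve secondary and follow-up outcomes only.

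Then bring the other sections into line with Sample size, Inclusion criteria and Stage Two:
- Implementation practices and Proposed Timeline: separate the period of offering the test from the primary analysis window.
- Both paragraphs on comparison practices (Study design and Stage One): replace the reference to the trial's period with the dated window, and use the same dates in the data request.

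Practice-by-practice paired windows are not needed; the protocol describes the comparison practices only as similar.

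The cost is a wording amendment. It needs no new data, practices or women, because the sample size already rests on one year.

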#### **Comparison practices**

Seven similar Mahitahi primary care practices (the comparative practices) who will be business as usual offering cervical cytology screens will be asked for permission to retrospectively access their screening data. De-identified data for the same period as the implementation trial will be requested.

## **Data analysis**

**Primary outcome analysis:** comparing the screening coverage of two approaches.

1. Universal offer of HPV self-test approach
2. Offer of cervical cytology as per current approach

The two approaches will be compared using a Linear Mixed Model with a logit link, with practice fitted as a random effect. Non-inferiority for the primary outcome will be evaluated by observing whether the lower bound of the two-sided 95% confidence intervals for the difference in screening coverage between the two arms is above the non-inferiority limit of -10. If non-inferiority is evident, assessment as to whether the implementation has effectiveness superior to that of standard care will be carried out using the same approach but comparing to a zero difference. The primary analyses will be carried out on an intention-to-treat (ITT) basis. Per-protocol sensitivity analyses will also be conducted excluding participants who had major protocol violations. To account for any potential imbalance in underlying risk factors for screening uptake, sensitivity analyses will adjust for age, ethnicity, deprivation index, screening history and primary care practice.

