### **Stage One**

Four practices will be randomly selected from the 22 eligible practices that have a moderate to high proportion of Māori, and this random selection will be stratified by practice size and rurality. To do this the 22 practices will be divided into the following four population size by rurality groups: small-rural, small-urban, large-rural and large-urban. Within each of the population size by rurality groups, one practice will then be randomly selected using computer generated random numbers (which gives a total of four practices). The randomisation sequence will be generated by the trial statistician.

Consent to participate in the implementation will be sought from each of the four practices. If a practice does not consent, then another practice will be randomly selected that has the same population size by rurality group.

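### Practice size and rurality govern the draw of implementation practices but are in neither the primary nor the sensitivity models, and comparators are chosen on unnamed similarities

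*Protocol*

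**What the plan says.** **Selection of implementation practices.** For the first four practices, the protocol (Stage One) says "this random selection will be stratified by practice size and rurality". One practice comes from each of four size-by-rurality groups, and a practice that declines is replaced from its own group. For the further three (Stage Two), "The random selection will be stratified by practice size and rurality": one small-rural, one small-urban, and a third from the large practices with no split by rurality.

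**Selection of comparators.** The two Comparison practices sections and Stage Two ask only that comparators resemble the implementation practices. The traits are never named. Practices are approached until enough have given permission to use their data; no random draw is described.

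**Models.** The primary analysis (Data analysis) is "The two approaches will be compared using a Linear Mixed Model with a logit link, with practice fitted as a random effect". To deal with possible imbalance in risk factors for uptake, "sensitivity analyses will adjust for age, ethnicity, deprivation index, screening history and primary care practice". Size and rurality appear in neither place. The protocol writes out both lists itself, so this is a stated choice and not a detail left for a later analysis plan.

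**The concern.** The protocol treats size and rurality as important enough to steer which practices enter the implementation arm, then drops them from the comparison. The listed terms do not stand in for them:

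- A practice random effect does not remove differences between size and rurality groups. It counts them as between-practice noise.
- Listing practice again as a sensitivity covariate adds nothing. As a random effect it is already in the primary model. As a fixed effect it is aliased with approach, because each practice belongs to one arm throughout the comparison year.
- The other listed covariates describe women, not practices.

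What is at stake depends on the comparators. If they match the implementation practices on size and rurality, the interval is wider than it need be. If they do not, the estimated difference in coverage is partly a difference between kinds of practice, in a non-inferiority comparison of seven against seven.

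**Working it through.** **Inputs from the protocol (Sample size).** "will give 95% power at a one-sided significance level of 2.5% to detect a non-inferiority margin of 10% between the two groups"; "we assumed a screening rate of 72.5% in the comparative data and 72.5% in the participating practices"; "an average practice size of 400 participants and intra-cluster correlation coefficient of 0.01"; "A total of fourteen practices and 5600 women", that is 7 practices of 400 per arm.

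**Assumption, not in the protocol.** R is the share of between-practice variance explained by size and rurality. It is shown from 0 to 75%.

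**Step 1: reproduce the stated size.** Per arm without clustering: (1.960 + 1.645)² × 2 × 0.725 × 0.275 / 0.10² = 519 after rounding up. Design effect: 1 + 399 × 0.01 = 4.99. Product: 519 × 4.99 = 2590 women, or 2590 / 400 = 6.47 practices, rounded up to 7 practices and 2800 women. The stated size reproduces after rounding to whole practices. Power by the normal approximation is Φ(0.10 / 0.02666 − 1.96) = 96.3%.

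**Step 2: variance of a practice's coverage.**
- Between practices: 0.01 × 0.199375 = 0.001994.
- Within practices: 0.99 × 0.199375 / 400 = 0.000493.
- Between-practice share: 0.001994 / 0.002487 = 80%.

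**Step 3: cost of adjusting if it does not help (R = 0).** SE = √(2 × 0.002487 / 7) = 2.67 points.
- 12 df: half-width 2.179 × 2.67 = 5.81 points; power from the noncentral t, 93.0%.
- 10 df (size and rurality added): half-width 2.228 × 2.67 = 5.94 points; power 92.1%.
- Ratio of widths: 5.94 / 5.81 = 1.02.

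**Step 4: adjusted analysis by formula.** SE = √(2 × [0.001994 × (1 − R) + 0.000493] / 7), which is 2.38 points at R = 25% and 2.06 at R = 50%. On 10 df the half-widths are 5.31 and 4.60.

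**Step 5: like-for-like comparison under balance.** With balanced arms and R above 0, the true SE of the contrast is already the smaller figure in Step 4 without adjustment. The unadjusted model simply fails to report it. The comparison therefore has to be made at the same R. It was simulated with 40,000 trials per cell, linear regression on practice proportions, 400 women in every practice, and the same mix in each arm (two small-rural, two small-urban, two large-rural, one large-urban). Half-widths are means over simulated trials, so they lie slightly below the formula values. Type I error is one-sided, at a true difference of −10 points.

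| R | Half-width, unadjusted / adjusted (points) | Power, unadjusted / adjusted | Type I error, unadjusted / adjusted |
|---|---|---|---|
| 0 | 5.7 / 5.8 | 93.2% / 92.1% | 2.5% / about 2.5% |
| 25% | 5.8 / 5.2 | 94.1% / 96.5% | 1.4% / about 2.5% |
| 50% | 5.9 / 4.5 | 96.0% / 99.1% | 0.6% / about 2.5% |
| 75% | 6.0 / 3.7 | 98.0% / >99.9% | 0.1% / about 2.5% |

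At R = 50% the unadjusted model reports an SE of 2.76 points where the true value is 2.06.

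**Step 6: one illustration without balance.** Suppose the comparators were one small-rural, one small-urban, two large-rural and three large-urban, with coverage rising across those four groups (relative levels −1, −0.3, 0.3, 1). The group means are −0.143 for implementation and 0.329 for comparison, a gap of 0.471. The implementation practices' standard deviation on this scale is 0.678, so the gap is 0.471 / 0.678 = 0.695 standard deviations of the size-and-rurality effect. The bias is 0.695 × √(R × 0.001994): 1.6 points at R = 25% and 2.2 points at R = 50%, against the implementation arm. Simulated unadjusted power falls from 93% (R = 0) to 84% and 79%. With the group effects reversed, the bias would be the same size in the implementation arm's favour.

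**The case against.** Four points on the other side have force.

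1. **A reader might infer that comparators are matched on size and rurality, so that the design has already removed both from the contrast.** The protocol does not say so. It asks for resemblance on unnamed traits. Only the implementation draw is controlled, and not fully, given the seventh practice. The statement that the interval is too wide therefore holds only if the comparators turn out balanced.
2. **The stratification is of sampling, not allocation.** No practice is randomised between arms, so the usual rule that stratification factors of a randomisation belong in the analysis does not carry over directly. The case for adjustment rests on precision and on confounding.
3. **A reader might set 93.0% unadjusted power against 96.5% and 99.1% adjusted, a gain of up to six points.** That takes the baseline at R = 0 and the comparison at R = 25% or 50%. At equal R the gain is 96.5 − 94.1 = 2.4 and 99.1 − 96.0 = 3.1 points. The clearer gain is in interval width.
4. **Under balance the unadjusted analysis errs on the safe side.** Its type I error lies below 2.5% and its power is about 93% or more. With 14 practices, a sparse primary model is defensible.

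All four stand as limits on the claim. None explains why the sensitivity analyses, whose stated purpose is to handle imbalance in risk factors, leave out the two factors used to select practices. The first makes that omission matter more, because unmatched comparators bring bias and not only width.

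**Conclusion.** The point holds in a limited form. Size and rurality steer the implementation draw, are absent from both fixed model lists, and cannot be recovered through the practice term.

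- **If the comparators happen to be balanced**, the cost is precision. At an assumed R of 25% / 50%, the interval is about 0.6 / 1.4 points wider on each side than it need be, with 2 to 3 points of power forgone, and the test is conservative.
- **If they are not balanced**, practice-level confounding of unknown sign remains. The woman-level covariates may remove some of it, but there is no assurance that they do.

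The protocol does not support saying that the sample size is wrong or that a finding of non-inferiority would be unsafe for this reason. The figures rest on an ICC of 0.01, equal practices of 400 (the protocol gives 400 as an average), an assumed R, and a practice-level linear analysis standing in for the planned mixed model. At R = 0 adjustment gains nothing. The change is worth making because it is cheap and helps in either case, not because the trial fails without it.

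**What to change.** 1. In Data analysis, add practice size group (small/large) and rurality (rural/urban) as practice-level fixed effects to the primary model. If the sponsor prefers a sparse primary model, put them at least in a named sensitivity model. State small-sample degrees of freedom: 14 − 2 = 12 without the terms, 14 − 4 = 10 with them.
2. In the Comparison practices sections and Stage Two, name the traits on which comparators are chosen, and choose them within the same size and rurality groups as the implementation practices. Report the resulting mix by arm, including the rurality of the third Stage Two practice.
3. Remove practice from the list of sensitivity covariates, or say that it stays as the random effect.

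**Cost.** A line or two of text. Both factors must already be known for the eligible practices, since the draw uses them. If neither factor matters, the interval is about 2% wider (5.81 to 5.94 points) and power falls about one point (93% to 92%). Fitting all four groups instead of two additive terms leaves 9 df and power of about 91.5% in that case, so the additive form is the cheaper choice.

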### **Comparison practices:**

Four practices (but with similar characteristics to the implementation practices) will be asked retrospectively for permission to access data from records obtained through clinical care for comparison to the implementation practices. De-identified data for the same period as the implementation trial will be requested retrospectively. If a practice does not give permission to access data, another practice will be approached until four practices have given permission.

Any changes over time in this usual standard care for each practice will be documented.

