### **Data collection, extraction and management**

While Mahitahi will retain ownership of the data, the canSCREEN database will also serve as the primary source of research data relating to women who have an HPV test. The NSU is the best source of data regarding screening history and demographic information (sourced from the National Health Index). The practices will provide NHIs of participating women to the NSU to obtain information about screening history and clinical history at the start of the study time period, ethnicity, NZ Deprivation Index (socioeconomic status), and age (not date of birth). For participant safety reasons, and to be able to link to the NSU, restricted members of the research team will have access to the NHI of women in the implementation group. At the end of the implementation period, the research team will also request HPV vaccination status from the National Immunisation Register for women who participate in HPV testing. This is crucial information about expected HPV positivity and therefore provides important context for the findings related to triage, clinical care pathways and implementation. All data will be de-identified before data analysis.

The NSU will be the primary source of research data relating to women at participating practices who opt for cervical cytology rather than an HPV test, and for comparative data from non-participating practices. For these women, the practices will provide the NHIs of the eligible population of women to the NSU (minus the women who have had an HPV test) to obtain information about cervical cytology during the implementation time period, screening history at the start of the study time period, ethnicity, NZ Deprivation Index (socioeconomic status), and age (not date of birth). The practices will remove the NHI and provide the research team with the individual line data for analysis. If there are cases where the relevant information cannot be obtained from the NSU, demographic information will be obtained from the Ministry of Health National Health Index dataset.

Data for analysis will be stored on the secure Victoria University of Wellington server, in restricted access folders and password protected files. No individuals will be identifiable in the reporting of study findings.

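### The arms are not randomised, yet the unadjusted model decides non-inferiority and covariate adjustment is left to sensitivity analyses

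*Protocol*

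**What the plan says.** Implementation practices are selected at random within size-by-rurality groups, subject to consent. Under Stage One: "If a practice does not consent, then another practice will be randomly selected that has the same population size by rurality group". Stage Two adds three more by the same method.

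Comparison practices enter differently. Under Stage One: "Four practices (but with similar characteristics to the implementation practices) will be asked retrospectively for permission to access data". Under Stage Two: "An additional three practices with similar characteristics to the implementation practices will be asked for permission to retrospectively access data". Refusals are replaced by approaching other practices. No random step is stated for this arm, and no section allocates practices or women at random between the two approaches.

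The Data analysis section fixes the primary model: "The two approaches will be compared using a Linear Mixed Model with a logit link, with practice fitted as a random effect". It names no covariate. It then says that, because risk factors for uptake may be unbalanced, "sensitivity analyses will adjust for age, ethnicity, deprivation index, screening history and primary care practice".

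The covariates will be available. For women who are not HPV-tested at implementation practices, and for comparison practices, Data collection, extraction and management requests "screening history at the start of the study time period, ethnicity, NZ Deprivation Index (socioeconomic status), and age (not date of birth". The same items are requested for women who have an HPV test.

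**The concern.** Random selection of one arm makes that arm representative. It does not balance it against a second arm assembled by similarity and permission. A random practice effect allows for clustering and widens the interval, but it does not remove a systematic difference in case mix between the arms.

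The protocol itself treats age, ethnicity, deprivation and screening history as determinants of uptake and foresees imbalance in them. It still lets the model that ignores them give the non-inferiority verdict. If the two analyses disagree, the one more exposed to confounding prevails. Practice size and rurality, which governed selection of the implementation practices, appear in neither analysis. By contrast, the secondary outcomes, which are collected in implementation practices only, are to be stratified by or adjusted for three of these factors.

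Listing practice among the covariates adds a smaller problem: in the 12-month comparison each practice belongs to one arm only.

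**Working it through.** **Inputs.** From Sample size: 72.5% in both groups, margin 10 points, one-sided 2.5%, seven practices of 400 women per arm, intra-cluster correlation 0.01. From Table 1 (Northland, three years to March 2016): coverage 66.2% for Māori and 78.9% for European/Other. The between-arm difference in Māori share is an assumption, because the protocol gives none.

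**1. The plan's own power figure.**
- Individually randomised size for 95% power: 519 per arm.
- Design effect: 1 + (400 - 1) × 0.01 = 4.99.
- Inflated size: 519 × 4.99 = 2,590 per arm; 2,590 / 400 = 6.5, rounded up to 7 practices.
- SE at 7 × 400: sqrt(2 × 0.725 × 0.275 × 4.99 / 2800) = 0.0267.
- Power: Φ(0.10 / 0.0267 - 1.96) = 96.3%, or about 93% with t on 12 degrees of freedom.

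The stated 95% reproduces, so the sample size is not in dispute. It assumes no systematic difference between the arms.

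**2. Bias of the crude difference under an assumed imbalance.**
- Coverage gap: 78.9 - 66.2 = 12.7 points.
- Bias b = (difference in Māori share) × 0.127, treating the rest of the mix as European/Other.
- False non-inferiority at a true -10, if b favours implementation: Φ(b / 0.0267 - 1.96).
- Power at a true difference of 0, if b goes against implementation: Φ((0.10 - b) / 0.0267 - 1.96).

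| Assumed difference in Māori share | Bias (points) | False non-inferiority, bias favours implementation | Power, bias against implementation |
|---|---|---|---|
| 0 | 0 | 2.5% | 96.3% |
| 5 points | 0.6 | 4.3% | 94.0% |
| 10 points | 1.3 | 6.9% | 90.6% |
| 20 points | 2.5 | 15.7% | 79.9% |
| 30 points | 3.8 | 29.8% | 64.1% |
| 40 points | 5.1 | 47.8% | 45.4% |

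These are normal approximations. The 10- and 20-point rows are used below; the others show the range.

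**3. Practice as a covariate.** A design matrix with intercept, arm and 13 practice indicators has 15 columns and rank 14. With practice as a fixed effect, the arm effect cannot be estimated. With practice as a random effect, the model is estimable, but the term is already in the primary model and adjusts for nothing further.

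**The case against.** The design does something to limit imbalance. Comparators come from the same primary health entity, cover the same calendar period and are chosen to resemble the implementation practices. An adjusted analysis is prespecified for this very reason, so the dispute is over which of two planned analyses is primary. Nor do the documents point to a bias favouring implementation: Stage One draws implementation practices only from those with at least 15% Māori, which could just as well make the test conservative. All of this stands as a reason to expect that the bias may be small, and to show both directions. It does not settle the matter. Similarity is left undefined, there are only seven practices per arm, and the unadjusted estimate still decides.

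Three stronger readings are tempting but not supported.

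- **That the adjusted model cannot run.** This holds only if practice is a fixed effect. The protocol does not say so, and the primary model specifies it "with practice fitted as a random effect". On the natural reading the listing is redundant wording.
- **That the bias could plausibly reach half the margin through screening history.** A reader might set the 21% uptake in the earlier trial's control group against the 72.5% planning rate. A 10-point imbalance would then give 0.10 × (72.5 - 21) = 5.15 points and about 43% false non-inferiority (t, 12 degrees of freedom). The subtraction is not valid. The 21% is uptake of an offer, compared there with under-screened Māori women. The 72.5% is three-year coverage in all women, under-screened women included, so it is not the rate in the adequately screened.
- **That adjustment would remove the confounding.** It deals with measured factors only. Self-selection through consent and permission remains.

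**Conclusion.** The point holds as a matter of which analysis is primary. The between-arm comparison is not randomised, the decisive model is unadjusted, and the main measured determinants of uptake are planned to be available in both arms. An assumed 10- or 20-point difference in Māori share moves the crude difference by about half or nearly all of one standard error. Depending on direction, false non-inferiority becomes about 7% or 16%, or power becomes about 91% or 80%. These figures rest on the assumed imbalance, on 2016 coverage for two ethnic groups and on the planning standard error. They illustrate sensitivity and do not predict the bias in this trial. The listing of practice as a covariate is a wording fault to be cleared up, not proof that the analysis fails.

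**What to change.** - Make the covariate-adjusted model the primary analysis: screening history at the start, age, ethnicity and deprivation, plus practice size and rurality as far as 14 clusters allow. Keep practice only as the random effect.
- Standardise the adjusted logit-model result to a marginal coverage difference with its confidence interval. An adjusted logit coefficient is a conditional log odds ratio and cannot be set against the -10 margin directly.
- Report the unadjusted result as supportive.
- Delete practice from the list of adjustment covariates.
- State that adjustment covers measured confounding only.

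The cost is a change of wording, a standardisation step and a few between-practice degrees of freedom. With 14 - 2 = 12 available, the four size-by-rurality groups would take 3. No extra data are needed for the individual-level covariates.
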